#### T2 and T3 assessments

Following the completion of the T1 assessment, participants will commence the treatment condition to which they have been allocated (details of interventions provided below). Participants allocated to an active intervention group (PCIT-T or COS-P) will commence treatment as soon as possible, after which they will complete the T2 assessment (immediately post-treatment, i.e., 8 weeks after the T1 assessment), and the T3 assessment (4-months after the T2 assessment). Participants allocated to the Waitlist group will complete the T2 assessment at the end of the 8-week waiting period. The T2 and T3 assessments will be identical to that of the T1 assessment, except that the SSP will not be repeated at T2.

#### Participant reimbursement

As compensation for time and travel expenses, participants will be offered a $25 gift voucher and a small gift of appreciation for the child after completion of each of the assessments.

See Fig. 1 for a summary of participant flow through the study.

### Interventions

#### Parent-child interaction therapy – toddler (PCIT-T)

PCIT-T will be delivered according to the protocol outlined by Girard and colleagues [42]. This will include direct live coaching (from behind a one-way mirror using a ‘bug-in-the-ear’) during parent-child play sessions (CDI-T and PDI-T phases) at the KTC. Families will attend a CDI-T teaching session followed by 6–8 CDI-T coaching sessions and then a PDI-T teaching session followed by 2–4 PDI-T coaching sessions. All families in this condition will receive a total of 16 h of therapy. This will include 1–2 individual parent or parent-child sessions over an 8-week period (equating to two 45-min sessions most weeks and allowing for some weeks with one 45-min session). The PCIT-T treatments will be provided on-site at the KTC and delivered by experienced clinicians who have been trained and accredited in the intervention. Treatment fidelity will be maximized by the use of (i) post-session fidelity checklists, completed by PCIT-T clinicians at the end of every treatment session [42] and (ii) clinical reflective supervision sessions provided to each of the PCIT-T clinicians on a fortnightly basis throughout the course of the research trial by one of the PCIT-T program developers.

Circle of Security – Parenting™ (COS-P) will be delivered according to the protocol outlined by Cooper, Hoffman, and Powell [49]. COS-P is a manualized eight-session parent-education group program; it has the same broad aims and core components as the COS-Intensive model from which it was developed (i.e., to increase caregiver sensitivity and responsiveness to child cues, empathy for the child by supporting parental reflective functioning, recognition and understanding of child attachment cues, and awareness of the impact of the caregiver’s own attachment history on caregiving patterns). The program is facilitator led, and uses archived clinical DVD footage of problematic parent-child interaction and healthy alternatives to illustrate attachment patterns and parenting styles, and promote group discussion. All parents in this condition will receive a total of 16 h of therapy. This will include eight, 2-h, parent-only group sessions (childcare provided). The COS-P groups will be provided on-site at the KTC, co-facilitated by two clinicians who have been trained and accredited in the intervention, at least one of whom has experience in running previous groups and who has no training or experience delivering PCIT-T. In total, approximately 6 different therapists will be involved as facilitators for the COS-P groups. Treatment fidelity will be maximized by the use of (i) fidelity checklists, completed individually by each of the group facilitators at the end of each session, and (ii) 1-h clinical reflective supervision sessions, provided to the group facilitators twice during the course of each group program by an experienced COS-P facilitator and clinical supervisor.

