### Study aims and hypotheses

The objective of the current study is to evaluate the most recent iteration of the PCIT-T model, as articulated by Girard and colleagues [42]. Study aims will be to 1) examine whether the PCIT-T intervention leads to positive changes in parenting capacity for parents of young toddlers presenting with early disruptive behaviors; and 2) examine social-emotional, attachment and behavioral outcomes for children who participate in PCIT-T.

Three conditions will be tested: a waitlist control group who are not treated, PCIT-T and a group receiving Circle of Security – Parenting™ (COS-P), a group-based attachment-informed preventative parenting education program. COS-P was chosen as the comparison intervention because it is currently delivered as the parenting treatment of choice in many government and community-based settings across Australia [49] and is of a similar treatment length (8 weeks). It is acknowledged that COS-P is not a perfect comparator as PCIT-T is delivered individually while COS-P is delivered to groups of 6–8 participants. To address this, the treatments will be matched for treatment length (8 weeks) and total treatment time (16 h), and study results will be interpreted with the different delivery modalities in mind.

We expect that of the two interventions, PCIT-T will be associated with the greatest treatment gains for the following reasons: (i) PCIT-T is the more intensive treatment model (PCIT-T is delivered on an individual basis; COS-P is a group program), (ii) PCIT-T is targeted at a narrower age range and is therefore more developmentally tailored (PCIT-T is for children aged 12–24 months; COS-P does not specify a child age range), (iii) PCIT-T is designed specifically for children with clinically significant disruptive behaviors and COS-P is not, and (iii) compared to COS-P, PCIT-T has an explicit behavioral component, which aligns with meta-analytic findings indicating that interventions that are brief, have a behavioral component, and which enhance parental sensitivity are most likely to bring about lasting improvements in children’s attachment security and thus capacity for behavioral and emotional regulation [50].

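### The PCIT-T sessions described come to 7.5–10.5 h (12 h at most at 45 min each), not the stated 16 h, so the claimed match with COS-P on treatment time is unsupported

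*Protocol article*

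**What the plan says.** Under Study aims and hypotheses, the protocol article concedes that COS-P is an imperfect comparator because it is given in groups while PCIT-T is given individually. Its answer is that "the treatments will be matched for treatment length (8 weeks) and total treatment time (16 h"), with results read in the light of the different delivery modes.

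The PCIT-T paragraph under Interventions then describes the amount of treatment in three ways:

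- **Total:** "All families in this condition will receive a total of 16 h of therapy".
- **Session list:** "Families will attend a CDI-T teaching session followed by 6–8 CDI-T coaching sessions", and "then a PDI-T teaching session followed by 2–4 PDI-T coaching sessions".
- **Weekly pattern:** one or two sessions over an 8-week period, "equating to two 45-min sessions most weeks and allowing for some weeks with one 45-min session".

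The COS-P paragraph that follows gives the same total, "All parents in this condition will receive a total of 16 h of therapy", made up of eight parent-only group sessions of 2 h.

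**The concern.** The three descriptions of PCIT-T cannot all be true. Both the session list and the weekly pattern, at the stated session length, fall well short of the stated total. The COS-P sessions do add up to theirs.

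The 16 h figure carries weight because equal length and equal total time are the design features offered to offset the individual-versus-group difference. They concern the only active-versus-active contrast, which the Statistical analysis section plans at both T2 and T3. If the 45-min schedule is what families receive, half of that mitigation is missing. A finding of no difference, or of a COS-P advantage, could then partly reflect fewer hours of PCIT-T. The Discussion lists delivery mode as a limitation but not unequal contact time, so a reader would assume equal hours.

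**Working it through.** **Inputs** (Interventions section unless noted)

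- PCIT-T stated total: 16 h.
- PCIT-T sessions: 1 CDI-T teaching, 6–8 CDI-T coaching, 1 PDI-T teaching, 2–4 PDI-T coaching.
- PCIT-T session length: 45 min = 0.75 h. Frequency: at most two a week for 8 weeks.
- COS-P: eight sessions of 2 h, stated total 16 h.
- Background description of PCIT-T: typically 10–12 sessions of 30–40 min, and 5 min of daily home practice.

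**Formula:** hours = number of sessions × session length.

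**The stated totals**

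- COS-P: 8 × 2 h = 16 h. This reproduces.
- PCIT-T by the session list: fewest 1 + 6 + 1 + 2 = 10, most 1 + 8 + 1 + 4 = 14. Hours: 10 × 0.75 = 7.5 to 14 × 0.75 = 10.5. The 16 h is not reproduced.
- PCIT-T by the weekly pattern: ceiling 8 × 2 × 0.75 = 12 h, reached only if no week has a single session. Taking two sessions in at least 5 of the 8 weeks and one in the rest (my reading of the weekly pattern) gives 13–16 sessions, or 9.75–12 h. Again, 16 h is not reproduced.

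**Shortfall against 16 h**

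| Basis | PCIT-T hours | Shortfall | As % of 16 h |
|---|---|---|---|
| Weekly ceiling | 12 | 16 − 12 = 4 h | 4/16 = 25% |
| Session list, most | 10.5 | 16 − 10.5 = 5.5 h | 5.5/16 = 34% |
| Session list, fewest | 7.5 | 16 − 7.5 = 8.5 h | 8.5/16 = 53% |

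**What 16 h would require**

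- At 45 min: 16/0.75 = 21.3 sessions, or 21.3/8 = 2.7 a week.
- With 14 sessions: 960/14 = 69 min each. With 10 sessions: 960/10 = 96 min each.
- With 16 sessions: 960/16 = 60 min each. The list stops at 14 sessions.

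**Readings that might rescue the total**

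- *Longer teaching sessions.* The 8–12 coaching sessions use 6–9 h, so the two teaching sessions would each have to last (16 − 9)/2 = 3.5 h to (16 − 6)/2 = 5 h.
- *Counting home practice.* 56 days × 5 min = 280 min = 4.7 h. Added to the 14-session maximum, this gives 10.5 + 4.7 = 15.2 h, still below 16 h. It would pass 16 h only with 16 sessions (12 + 4.7 = 16.7 h), more than the list allows. Home practice is also not therapy delivered by a clinician.
- *Counting assessments.* T1 comes before treatment starts and T2 after it ends.
- *The typical course in the Background.* 10 × 30 min = 5 h to 12 × 40 min = 8 h, further from 16 h.

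**The case against.** The best counter-argument is that the article shows an inconsistency, not a real imbalance in treatment. The PCIT-T sentence is visibly garbled: read literally, it promises one or two sessions in 8 weeks, so a weekly qualifier has evidently dropped out. The session length could be a slip too, since sixteen 60-min sessions would give exactly 16 h. The sentence introduces the sessions as something the 16 h will include, which need not be exhaustive. The teaching sessions are given no length of their own, and delivery follows a treatment manual that is not shown.

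Part of this stands. The document does not reveal which figure is wrong, so every shortfall above depends on the 45-min schedule being the correct element.

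The rest does not bring the total to 16 h. The same introductory wording is used for COS-P, where the listed sessions are the whole 16 h. The 45-min length is applied to the individual parent or parent-child sessions with no exception for teaching, and no other contact is named. Nor is this a matter of an article leaving detail to a fuller document: it prints the total, the count, the length and the frequency, and they disagree.

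A second argument is that the consequence is small. An hour of individual coaching and an hour in a group of 6–8 are not the same dose even when matched, PCIT-T is mastery-based so hours would vary anyway, and a PCIT-T shortfall would work against the study's hypothesis. These points limit the damage and are accepted. They do not support a claim of matched total time that the stated schedule contradicts.

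**Conclusion.** The concern holds. As written, PCIT-T comes to 7.5–10.5 h by its session list and at most 12 h by its weekly pattern, against 16 h stated and 16 h for COS-P. The match on total treatment time is therefore unsupported.

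These sizes assume that 45 min applies to all PCIT-T sessions, teaching included, and that no unlisted therapy contact exists. If instead the 16 h is right, the error lies in the session number or length and the match can be restored on paper.

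The reach is limited. The 8-week match, the contrasts with waitlist and the sample size calculation are unaffected. Fewer hours could not explain a PCIT-T advantage over COS-P. They matter for interpreting a null or reversed result in that comparison at T2 or T3.

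**What to change.** Establish which PCIT-T figure is right, then do one of the following.

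- **If 16 h is right:** correct the number and length of sessions in the PCIT-T paragraph so that they total 16 h.
- **If the 45-min schedule is right:** replace 16 h in the PCIT-T paragraph and in Study aims and hypotheses with the true planned hours. Delete the claim of matching on total treatment time and keep the 8-week match. Report attended hours by arm from session records, and interpret PCIT-T versus COS-P as a comparison of the programmes as delivered.

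The first option costs a text correction. The second adds a tabulation of attended hours. Clinicians in both arms already complete a fidelity checklist after every session, which gives a record to build on.

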#### Waitlist

Participants allocated to this condition will complete the T1 assessment but will receive no treatment for the following 8-week period. They will then complete the T2 assessment, and this will represent the completion of their participation in the study. Families allocated to the waitlist condition will be offered the opportunity to receive PCIT-T or COS-P (whichever they choose) at the completion of the T2 assessment but this will not be for the research trial.

### Measures

For a summary of study measures, see Table 1. For all observational measures, coding will be conducted by a primary coder and 25% of cases double-coded by a second coder to ensure inter-rater reliability. All coders will be masked to treatment condition and assessment time point.

**Table 1 Tab1:** Summary of key study variables and measurement tools, and assessment time points administered

Variable	Measure	Time 1	Time 2	Time 3^a^
*Parenting capacity outcomes*				
Positive parenting	Dyadic Parent-Child Interaction Coding System – Labeled Praise	✓	✓	✓
Negative parenting	Dyadic Parent-Child Interaction Coding System – Negative Talk	✓	✓	✓
Parenting sensitivity	NICHD Study of Early Child Care and Youth Development: Sensitivity Scales	✓	✓	✓
Sense of competence in managing negative toddler emotions	Coping with Toddler’s Negative Emotions Scale (CTNES)	✓	✓	✓
Caregiving helplessness	Care-Giving Helplessness Questionnaire (CHQ) - ‘mother helpless’ subscale	✓	✓	✓
Risk of abuse	Brief Child Abuse Potential Inventory (BCAP)	✓	✓	✓
Mentalizing about the child	Mind-mindedness rating system	✓	✓	✓
Emotion regulation	Difficulties in Emotion Regulation Scale (DERS)	✓	✓	✓
Parenting stress	Parenting Stress Index–Short Form (PSI-SF)	✓	✓	✓
*Child outcomes*				
Social-emotional functioning	Devereux Early Childhood Assessment (DECA)	✓	✓	✓
Child emotion regulation maturity	Observational 5-min ‘child frustration task’	✓	✓	✓
Attachment security	Attachment Q-sort (AQS)	✓	✓	✓
	Strange Situation Procedure (SSP)	✓	✗	✓
Child externalizing behaviour	Child Behavior Checklist (CBCL/1.5–5)	✓	✓	✓

^a^ Time 3 measures only administered to participants in the PCIT-T and COS-P groups

*Positive and negative parenting* during the 20-min parent-child interaction will be coded according to the Dyadic Parent-Child Interaction Coding System, Fourth Edition, a coding scheme designed to rate parent-child verbal interactions and responses during observed interactions [52]. The DPCIS has been shown to have high levels of reliability, with kappa coefficient scores typically over .80 [53, 54]. Trained DPICS coders will view the video-recorded parent-child interaction sessions, create a moment-by-moment transcript of the parent-child interactions, and use the transcription and video to code every parent verbalization. A ‘positive parenting’ score (total number of labeled praises) and a ‘negative parenting’ score (total number of negative statements) will be calculated based on the number of times these verbalisations are observed during the five structured situations. To create standardized scores, frequency counts will be transformed into ratios based on the following: 1) total number of labelled praises divided by total number of verbalisations, and 2) total number of negative statements divided by total number of verbalizations.

*Parenting sensitivity* during each episode of the 20-min parent-child interaction will be coded using the NICHD Study of Early Child Care and Youth Development: Sensitivity Scales (NICHD-SECCYD) [55]. This coding system has demonstrated reliability (intra-class coefficents typically .8 and over [56, 57]) and validity (positive associations with infant attachment quality [56–58], and sensitivity to change following parenting interventions [59]). The NICHD-SECCYD sensitivity scales yields a composite parental sensitivity score, calculated by summing scores on six scales, each scored on a 4-point scale whereby higher scores indicate that the variable is more characteristic of the parent: sensitivity, positive and negative (reversed) regard for the child, intrusiveness, respect for autonomy and hostility (reversed).

*Parental sense of competence in managing negative toddler emotions* will be assessed using the Coping with Toddler’s Negative Emotions Scale (CTNES) [60]. The CTNES comprises 12 hypothetical scenarios in which the child becomes upset, angry, or distressed. The caregiver is asked to rate their likelihood of engaging in each of seven possible responses to their child’s negative emotions: (a) distress reactions, (b) punitive reactions, (c) minimizing reactions, (d) expressive encouragement, (e) emotion-focused reactions, (f) problem-focused reactions, and (g) granting the child’s wish. For each scenario, caregivers rate each possible response from 1 (very likely) to 7 (very unlikely). Previous studies have shown the CTNES to have a high level of internal consistency (alphas for individual subscales ranging from .68–.93) and test-re-test reliability (*r*s = .65 to .81) [60].

*Parent sense of caregiving helplessness* will be assessed using the Caregiving Helplessness Questionnaire (CHQ) [61] (‘mother helpless’ subscale). The scale comprises 7 items, each answered on a five-point scale, with higher scores indicating greater helplessness. The helplessness subscale of the CHQ has been shown to possess good construct validity and to be internally consistent (αs .80–.85) [44, 62].

*Parent mentalizing about the child, operationalized as mind-mindedness,* will be coded from the speech sample question (“What is your child like?”), obtained during the home visit. Coding will be conducted according to Meins and Fernyhough’s mind-mindedness coding guidelines [63]. Participant responses will be transcribed verbatim from audio-tape and then the primary coder will section the transcription into individual comments, based on temporal (1-s gap) or semantic discontinuities. Each individual comment will then be coded as belonging to one of five categories, namely ‘Mental’, ‘Behavioral’, ‘Physical’, ‘General’, ‘Self-referential’). Comments coded as ‘Mental’ attributes will be descriptors related to the child’s mental life, intentions, interests, likes and emotions. Behavioral attributes will be comments that refer to the child’s behavior (e.g., games or activities that the child does). Physical attributes will be comments about the child’s appearance, position in the family or age, and general attributes will include comments that don’t fit into the other three categories. The self-referential code will be given when the parent speaks about themselves, rather than the child. A ‘mental state’ frequency score will be calculated as the frequency count of ‘mental’ comments as a proportion of the total number of verbalisations, to control for verbosity. Meins’ coding system for mind-mindedness has been well validated, with previous studies showing good inter-rater reliability and stability over time (e.g., McMahon and colleagues reported intraclass correlations for individual categories ranging from .89–.92 and showed that mothers who made more mind-related comments at 7 months postpartum, also did at 19 months) [64]. Construct validity has also been demonstrated with higher mind-mindedness scores having been shown to predict maternal sensitivity [65] and infant attachment [27].

*Parental emotion regulation* will be assessed using the Difficulties in Emotion Regulation Scale (DERS) [66], a 36-item, self-report measure of emotion dysregulation. The DERS yields a total score (range 36–80, higher scores indicating greater emotion dysregulation) and six subscale scores: (1) Nonacceptance of emotional responses, (2) Difficulties engaging in goal directed behavior, (3) Impulse control difficulties, (4) Lack of emotional awareness, (5) Limited access to emotion regulation strategies, and (6) Lack of emotional clarity. The DERS has been shown to have high internal consistency (α = .93), good-test retest reliably (intra-class correlation coefficient = .88), and adequate construct and predictive validity [66].

*Parenting stress* will be assessed using the Parenting Stress Index–Short Form (PSI-SF), a 36-item self-report measure of stress in the parent–child system [67]. The PSI-SF comprises three subscales: ‘Parental Distress’, ‘Parent–child Dysfunctional Interaction’, and ‘Difficult Child’, with higher scores indicating greater dysfunction. The internal consistency (α = .71–.92), test re-test reliability α = .06–.80), and convergent validity of the PSI-SF subscales and the total score have been demonstrated in a similar sample of English-speaking parents of young toddlers with behavioral problems [68].

*Child abuse potential* will be assessed using the Brief Child Abuse Potential Inventory (BCAP) [69]. The BCAP is a parent-report scale that comprises 24-items, each rated as ‘agree’ or ‘disagree’. The BCAP is an abbreviated version of the widely-used 160-item Child Abuse Potential Inventory [70]. Internal consistency (α = .89) and construct validity have been demonstrated [69].

*Child social-emotional functioning* will be assessed using the Devereux Early Childhood Assessment (DECA) [71, 72], a strengths-based parent-report scale designed to assess emotional, social, and behavioral capacities during early childhood. There are two aged-based versions of the DECA, an infant version (DECA-I; designed for ages 1–18 months; 33 items) and a toddler version (DECA-T; designed for ages 18–36 months; 36 items). The DECA-I comprises two scales (initiative, attachment/relationships) and a Total Protective Factors scale, which is a composite of the initiative and attachment/relationships scales. The DECA-T comprises three subscales (initiative, attachment/relationships, self-regulation) and the Total Protective Factors composite. In this study, participating children will complete the DECA-I or DECA-T depending on their age. The DECA-I and DECA-T subscales, rated by parents, have been shown to be internally consistent (total protective factors α = .90–.94), to show good test-retest reliability (*r*s = .71–.99) [72].

*Toddler emotion-regulation maturity* will be rated from videotapes of the 5-min ‘toddler frustration task’ using the coding protocol developed by Johnson [51]. This will involve first, the level of distress shown by the toddler being coded in 30 × 10 s intervals, on a four-point scale incorporating both intensity and duration of distress, with higher scores indicating a higher level of distress. Scores will be summed to yield a total toddler distress score (possible range 0–90). Second, regulatory behaviors articulated by Calkins et al., [73] (attentional deployment, situation modification and cognitive change) will be coded on a four-point scale during the same time intervals. Based on Gross’ (2007) theoretical framework for the developmental hierarchy of emotion-regulation strategies [74], these regulatory behavior scores will be arranged hierarchically into three scales reflecting least mature (attentional deployment) to most mature (cognitive change) regulatory strategies and summed to yield a composite emotion-regulation maturity score. Maternal support seeking will also be coded in the same way as regulatory behaviors and will be examined as a separate scale.

*Child attachment security* will be assessed in two ways so that both dimensional and categorical ratings can be obtained. First, to examine attachment security dimensionally, the video-taped home visit will be coded using the Attachment Q-sort (AQS) [75, 76], a validated coding procedure designed to assess attachment security in a naturalistic environment in children aged 12–48 months. In the AQS, various descriptors of child behavior, including attachment behavior, are sorted into nine piles from “most characteristic” to “least characteristic.” An overall security score is derived by correlating the sort for each child with a criterion sort of the prototypical behavior of a secure child. Second, to examine attachment security categorically, including disorganization, child behavior observed during the SSP will be coded according to the coding systems of Ainsworth [15] and Main and Solomon [17]. The SSP has demonstrated validity [13, 77] and is widely considered to be the gold standard measure of infant attachment. The SSP comprises eight three-minute episodes involving separations and reunions between the mother, the child and a friendly stranger. Infants are subsequently assigned to one of three ‘organized’ classifications based on their observed behavior, namely secure (B), anxious-avoidant (A), or anxious-resistant (C), following the Ainsworth coding system [15]. In addition, a primary ‘disorganized’ (‘D’) classification can also be applied with the ABC classifications as secondary, using procedures described by Main and Solomon [17]. SSP coding will be conducted by coders who have undertaken a 10-day training and been certified as a reliable coder by attaining at least 80% agreement with a SSP trainer.

Parent-reported *externalizing child behavior* will be assessed using the Child Behavior Checklist for ages 1.5–5 years (CBCL/1.5–5) [78], a validated parent/teacher report scale designed to measure behavioral, emotional and social functioning in children aged 1.5–5 years, and which has been used reliably with children as young as 12 months [46, 79]. The CBCL/1.5–5 comprises 99 items, each rated in terms of the frequency with which the child displays given problem behaviors on a scale of 0–2 (higher scores indicating presence of the behavior). CBCL scores can be summed to yield a ‘total problems’ score and an externalizing sub-scale score can also be computed. In the current study, the parent report version of the CBCL/1.5–5 and the externalizing sub-scale score will be used.

